## **1. BACKGROUND**

### **1.1 Pandemic rapid response.**

The Foundation for the Advancement of Family Medicine and the Foundation of the Canadian Medical Association have identified an urgent need to develop novel approaches to addressing outcomes of the COVID-19 pandemic. They are consequently financing the Co-RIG Program Phase 1, designed to support practice innovations that reduce the direct or indirect harms of COVID-19 and target family practice innovative interventions that are likely to have a measurable, positive impact on patients and/or populations within 6 months of the start of funding. This protocol is a response to that mandate.

### **1.2 Mental health of older adults and their caregivers during the COVID-19 pandemic.**

During the COVID-19 pandemic, older adults with chronic physical conditions are a particularly vulnerable population for unmet mental health needs. Depression and anxiety are several-fold more prevalent in this population in comparison to counterparts without chronic conditions, and may be even higher during the pandemic. The pandemic containment measures are also likely to exacerbate pre-existing problems with detection of mental health conditions in older adults. Anxiety appears to be the most prevalent emotional response within the pandemic.

### **1.3 Telephone supported self-care interventions for mental health problems.**

With the COVID-19 pandemic, there has been a rapid deployment of telehealth. For older adults, the telephone remains the most reliable telehealth modality, because they experience more difficulty and make more errors in completing online tasks than their younger counterparts due to age-related cognitive and motor function impairments. Telephone-supported strategies are a promising avenue for expanding access to mental health care for older adults with chronic physical conditions, with potential for increasing quality of life, reducing healthcare expenditures, and promoting independence in activities of daily living.

Worldwide, self-care interventions are recommended as the first level in a stepped care program for managing and treating mild-to-moderate depression and anxiety. Meta-analyses affirm that guided self-care interventions and face-to-face psychological therapies for depression and anxiety have comparable effects, and that supported (or guided) self-care is more effective than unsupported. Our team has conducted two RCTs of telephone-supported mental health self-care interventions comprising a cognitive-behavioral therapy (CBT) skills-building toolkit and lay telephone coaching. The RCTs concluded that, compared to the self-care toolkit alone, telephone guidance from a lay coach improved adherence and clinical outcomes in middle-aged and older adults with chronic physical conditions and comorbid depressive symptoms (DIRECTsc).

Among cancer survivors with depression frequently accompanied by anxiety (CanDIRECT), a similar guided self-care intervention improved 6 month depression and anxiety symptoms, as well as mental health-related quality of life. Given this strong evidence base and the success of deploying the intervention in two large, funded RCTs, our proposal is to evaluate the delivery of a shortened, adapted intervention in real-world conditions in a cohort of vulnerable community-based older adults (65+ years).

## **2. RESEARCH OBJECTIVES**

We will assess and compare in a Randomized Control Trial (RCT) two self-care intervention strategies with 8-week follow-up:

1. The feasibility of delivering the interventions during the pandemic;

2. The acceptability of the interventions for patients;
3. The acceptability of the interventions for family physicians.
4. The effectiveness of the interventions on severity of symptoms of depression and anxiety at 8 weeks.

Criteria for success for feasibility include measures of recruitment, retention and fidelity of intervention delivery: at least 75% of patients will agree to participate; at least 75% will complete the 2-month follow-up and at least 85% of the intervention components will be delivered as per the intervention protocol (see description of checklist further below). Success regarding acceptability outcomes: at least 75% will use the self-care tools; at least 75% of those assigned to receive coaching will complete 3 calls; and at least 75% in both groups will have a positive satisfaction score at 2 months (Client Satisfaction Questionnaire (CSQ) score of at least 75%).

### **3. METHODS**

#### **3.1 Study Design and timeline**

We will conduct a single blind, individually randomized, pilot trial of 2 self-care strategies to address symptoms of depression and anxiety (either premorbid or resultant from the pandemic) among home-based seniors with chronic physical conditions. The strategies to be tested are 1) validated self-care tools (internet and paper-based) plus up to 3 telephone coach calls; 2) self-guided tools alone. The trial design adheres to the CONSORT criteria, the CONSORT extension for pragmatic trials, and guidelines for behavioral trials. The trial protocol is registered on clinicaltrials.gov.

Recruitment and follow-up will be conducted until the end of 2020, with results to be reported in early 2021. As mentioned in section 1.1, the funders have targeted immediate and short-term innovations that maximize the effectiveness of care for patients and are looking for projects to be completed within a 6-month timeframe.

#### **3.2 Sample and exclusion criteria**

We have already assembled a cohort of 267 patients 65+ years old for a previous study (PCAP study, see SMRC protocol #18-04). Among these, 80% (n=213) agreed to be contacted again for future research opportunities. These patients were discharged home following hospitalization between October 2018 and December 2019 at the medical or geriatric units of two general hospitals on the west island of Montreal. Among the original cohort, 40% were born outside Canada; 30% received homecare services, and 65% were high-risk for functional decline, death, and increased health care service utilization.

With anticipated 75% participation, we project a sample size of 160. Exclusion criteria for the current study will comprise: moderate to severe cognitive impairment (using BOMC a brief cognitive screen); unable to read in English or French (self-reported); hearing impairment (as judged by research staff); currently receiving counseling or psychological therapy (as these treatments may conflict with the self-care interventions); currently living in a long term care or other medicalized facility, or presenting suicidal intent (as identified through the final item of the PHQ-9 which will be asked at screening). Patients with suicidal intent will be contacted by the coach supervisor for further assessment and referral (see section 3.7 below). Patients receiving antidepressant or anxiolytic medications will be eligible for the study, as will all patients who do not meet the threshold for clinically-significant symptoms of depression and/or anxiety as they

may still benefit from the intervention Participants who begin counseling or psychological therapy after enrolment will not be withdrawn. Participants who are not eligible or interested in the study will be invited to contact 2-1-1 to follow-up on any needs (see [www.211qc.ca/en/](http://www.211qc.ca/en/)).

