### **3.4 Data collection from patient participants**

Following consent, RAs will conduct the baseline interview (see Appendix C) with participants. Measures to be collected are as follows:

- Symptoms of depression: We will use the PHQ-9, a widely used 9-item measure of depression severity to determine presence and type of depressive symptoms. The PHQ-9 was selected based on its wide use in medical populations, established severity ranges and sensitivity to change, validation as a screening measure, and inclusion of somatic symptoms which are recognized as a core domain of depression, not confounding diagnosis in patients with chronic disease. The criterion for clinically-significant depression is 10 (but as specified above, this is not being used as an eligibility cut-point).
- Severity of anxiety symptoms: The seven item GAD-7 will be used as a continuous measure of severity of anxiety symptoms (internal consistency: Cronbach  $\alpha = .92$ ; test-retest reliability: intraclass correlation=0.83). Scores range from 0-21. The criterion for clinically-significant anxiety is 10 (also not used as an eligibility cut-point)
- Alcohol abuse: The 4 item CAGE questionnaire with a score ranging from 0-4 will be used to detect alcohol abuse and dependence. Although a cut point of 2 or more is used conventionally (average sensitivity 0.71, specificity 0.90), the cut point of 1 or more results in greater sensitivity as expected, and has been used in some studies. We will categorize as: no, possible (score of 1), or probable (score of 2+).

- Other baseline data: include questions on hospitalizations and ED visits during the previous 6 months, COVID diagnoses in patient or family, current living arrangement, having a family caregiver, and current homecare services.

At 8 weeks, with an anticipated follow-up rate of 75% (120 end of project interviews), the PHQ-9, and GAD-7 will be re-administered, along with enquiry into use of the self-care materials, perceived helpfulness in managing mental health problems, satisfaction with the intervention, and use of health services including any counseling or therapy started, during the 8-week study period. Satisfaction will be measured with a 3-item version of the Client Satisfaction Questionnaire (CSQ-3), highly correlated with the CSQ-8 ( $r=0.94$ ).

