### **3.5 Interventions**

The interventions to be evaluated in the RCT are: 1) the algorithm-determined self-care tools, matched to the specific mental health symptoms reported by participants, and 2) the tools plus up to 3 coach calls. All participants receive the self-care tools; only one group receives the coaching. This design allows us to evaluate the feasibility and acceptability of the tools, and the additional benefit (if any) of the coaching. Coaching is expected to increase use of the tools.

The tools and the coaching manual will be adapted from those we have successfully deployed in the DIRECTsc depression self-care project focusing on patients with depressive symptoms, but abbreviated to meet the needs of the proposed short-term intervention for a broader sample of patients to include those with anxiety symptoms and with minimal symptoms. Tools will include individual chapters of the Antidepressant Skills Workbook, the mood monitoring tool, a workbook on managing worry; relaxation audio files and information on exercise and healthy eating (see Toolkit contents described in Appendix D). In view of the short duration of the intervention (8 weeks), a maximum of 2 tools will be sent to each participant.

An algorithm will determine which self-care tools, matched to the specific mental health symptoms reported by participants, will be couriered to the participants. The study coordinator will apply the algorithm (using a paper form) to the participant's baseline results. An administrative assistant will be available at the Research Centre to assemble the required tools and arrange for them to be couriered to participants' homes using a secure courier service we have used in previous studies. Along with the tools, participants will be sent a welcome letter describing their study group assignment, and what to expect next (coach calls, if relevant, and expected timeline for the follow-up questionnaire).

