### **3.6 Randomization**

Participants will be randomized to Group 1 (tools only) or Group 2 (tools with coaching) by a computer-generated randomization schedule that uses random block sizes, with an allocation ratio of 1:1; SAS University Edition will be used. In order to ensure allocation concealment, the study coordinator will first verify eligibility and informed consent. Subsequently, the unique patient identifier (PID) from the recruitment log will be entered into the randomization schedule, along with: date of consent, date of baseline interview. An automated interface will then assign the participant to the study group. Participants will be stratified based on whether their symptoms are none to mild or moderate to severe to ensure an equal balance of symptom severity in both study groups. Participants will be categorized as none to mild if their PHQ-9 is less than 10 and their GAD-7 score is less than 10. Participants with a PHQ-9 score of 10 or more and/or a GAD-7 score of 10 or more will be categorized as being in the moderate to severe group.

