### **3.9 Data analysis and statistical power**

Data analysis will be conducted and reported according to CONSORT guidelines. All the quantitative analyses will be carry out with SAS University Edition, STATA 15.0 and R Cran software.

The feasibility of the study will be described using the data collected as part of the study log, recruitment, refusal and uptake rates, completion of surveys, and the rates of missing data will be calculated.

Descriptive analyses will compare characteristics of participants associated with participation and completion of follow-up. Incomplete outcome data will constitute an important aspect of our study. Our general approach will be based on intention-to-treat (ITT) and Inverse Probability Weighting (IPW) will be used to handle missing data. Two sensitivity analyses will be carried out to validate the results obtained by IPW: 1) inclusion of subjects with complete data only; and 2) use of multiple imputation (MI) for missing data. Unless the primary outcome analyses yield different results for completers or MI vs IPW, the secondary analyses will be restricted to completers only.

Baseline imbalance will be assessed by comparing participants randomized to the 2 study arms with respect to 6 pre-specified baseline variables (AGE, SEX, hospital admitted to, COVID-19 DIAGNOSIS, PHQ-9, GAD-7); a maximum of 3 variables with clinically significant differences across arms will be identified.

The comparison of continuous outcomes between intervention and control groups will be based on a simple t-test; linear regression will be used to adjust for baseline imbalance (see above). Similarly, for binary outcome variables (CSQ), Pearson chi-square test and logistic regression will be performed. Effect sizes and 95% confidence intervals (95% CI) will be computed for all the analyses with a continuous outcome, and odds ratio and 95% CI for binary outcomes.

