#### Sample size considerations:

For continuous outcomes (PHQ-9, and GAD-7), a total sample size of n=120 patients will allow us enough power (80%) to detect at least a moderate Cohen's effect size (0.52) between the 2 intervention groups (group equal size, 2-tailed test and alpha 0.05). For the binary outcomes CSQ (75%+) with the same sample size and power, a minimum difference between the two study groups of 20-26% can be detected

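### Severity is stratified at randomisation but unused in the section 3.9 outcome analysis, so a null pooled difference in a low-symptom sample would be hard to interpret

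*Protocol*

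**What the plan says.** - **Who enters.** Protocol section 3.2 admits people below the symptom cut-points: "as will all patients who do not meet the threshold for clinically-significant symptoms of depression and/or anxiety as they" may still gain from the intervention. Section 3.4 repeats for the PHQ-9 cut-point of 10, "but as specified above, this is not being used as an eligibility cut-point", and says the same for the GAD-7. Section 3.5 describes the sample as broadened "to include those with anxiety symptoms and with minimal symptoms".
- **The scale.** For the GAD-7, section 3.4 gives "Scores range from 0-21", so there is a hard floor at zero. The PHQ-9 is likewise bounded below.
- **Randomisation.** Section 3.6: "Participants will be stratified based on whether their symptoms are none to mild or moderate to severe". The upper stratum is PHQ-9 of 10 or more and/or GAD-7 of 10 or more.
- **Analysis.** Section 3.9: "The comparison of continuous outcomes between intervention and control groups will be based on a simple t-test". Linear regression is added only to correct for imbalance. At most three covariates are allowed, picked from six candidates because they differ between arms. The randomisation stratum is not one of the six, and no by-stratum estimate is described.
- **Power.** With 120 analysed, equal groups, two-sided alpha 0.05 and 80% power, the trial can "detect at least a moderate Cohen's effect size (0.52) between the 2 intervention groups".

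**The concern.** Objective 4 is the effect on symptom severity. A participant who would score 0, 1 or 2 at 8 weeks with the tools alone has almost no room to show a further fall from coaching. The more such participants there are, the smaller the pooled difference that a given benefit can produce. A pooled null would then fit two accounts: coaching did nothing, or coaching helped where the scale could register it and the rest of the sample diluted the average.

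The protocol already holds the variable that would help tell these apart. It randomises within severity strata and then drops the stratum at analysis. The covariate rule makes this worse. PHQ-9 and GAD-7 are among the six candidates, but they enter only if the arms differ on them, and stratifying on severity makes that less likely. A factor likely to predict the 8-week score is therefore likely to be left out of the model, at a cost in precision.

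**Working it through.** **1. The plan's own figure.** Inputs from section 3.9: 120 analysed, so 60 per arm; two-sided alpha 0.05; 80% power. Normal approximation: d = (1.96 + 0.84) × √(2/60) = 0.51. The t-test gives 0.516, and power at d = 0.52 is 80.6%. The stated 0.52 is reproduced. The numbers leading to it also agree: 213 × 0.75 ≈ 160 and 160 × 0.75 = 120.

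**2. What a floor does to the achievable difference.** The documents give no mean, SD or share near zero, so these inputs are assumptions: skewed 8-week PHQ-9 scores (negative binomial, capped at 27) with three mean/SD pairs. Each person's score is lowered by 0.52 × SD but not below zero. The resulting d is then put into the two-sample t-test with 60 per arm.

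| Assumed mean (SD) | Scoring 2 or less on tools alone | Shift = 0.52 × SD | d after the floor | Power |
|---|---|---|---|---|
| 4 (4.2) | about 47% | 2.2 | 0.40 | 59% |
| 5.5 (4.9) | about 33% | 2.5 | 0.44 | 67% |
| 7 (5.4) | about 21% | 2.8 | 0.47-0.48 | 73% |

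The floor alone, with coaching acting on everyone, costs roughly 7 to 21 points against 80%.

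**3. Does the 0.52 statement need a uniform effect?** No. The power of the t-test depends on the pooled mean difference and the SD, not on how individual effects are spread. With the same three distributions and a proportional reduction of 34-44%, which is far from uniform in points, pooled d is 0.52 and simulated power is 82-83%.

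**4. What the stratum buys in the pooled model.** Adding the section 3.6 stratum to the linear regression removes between-stratum variance from the error term. In the floor scenario and in a 30% proportional-reduction scenario, pooled power rose by about 7-10 points, for example from 67% to 76%. This rests on the distributions above, a baseline to 8-week correlation of 0.6, and an assumed PHQ-9/GAD-7 correlation.

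**5. How precise the stratum estimates would be.** Under assumed distributions and PHQ-9/GAD-7 correlation, about 19 to 44 of 120 would fall in the moderate-to-severe stratum as section 3.6 defines it. With equal arms, the 95% CI half-width in within-stratum SD units is about 1.96 × √(4/n):
- n = 19: 1.96 × √(4/19) = 0.90
- n = 44: 1.96 × √(4/44) = 0.59
- pooled sample, n = 120, in overall SD units: 1.96 × √(4/120) = 0.36

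The smallest between-stratum difference in effect detectable with 80% power is (1.96 + 0.84) × √(2/(60f) + 2/(60(1 − f))), where f is the share in the upper stratum. It is lowest at f = 0.5: 2.80 × √(2/30 + 2/30) = 1.02 SD. An interaction test would therefore detect only very large differences.

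**The case against.** Several points on the other side stand.

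- **The power sentence is right.** A reader might infer that 80% power at 0.52 assumes every participant can move by that amount and needs a qualifier. It does not (step 3). The scenarios in step 2 lose power because their pooled effect is smaller than 0.52, and the protocol never claims to detect those smaller effects.
- **A far larger loss should not be blamed on the floor.** If only people with a baseline PHQ-9 of 10 or more benefit, by 0.52 of their own SD, pooled power falls to about 7-14% under the same assumptions. That comes from assuming no benefit below 10, including scores of 5 to 9 that have room to fall. Section 3.2 takes the opposite view of such patients. The calculation also uses PHQ-9 alone and so does not describe the section 3.6 stratum.
- **Effectiveness should not be read from the upper stratum.** That is tempting, but it would rest the conclusion on a few dozen people and replace the protocol's deliberately broad, pragmatic target. The and/or rule also admits people who are high on one scale and near zero on the other, so the stratum does not cleanly select room to move on each outcome.
- **The stakes are limited.** This is a pilot, effectiveness is listed fourth, and the numerical success criteria in section 2 concern feasibility and acceptability. Nothing says that a non-significant t-test means coaching adds nothing, and section 3.9 requires effect sizes with 95% CIs.
- **Subgroup detail can sit in an analysis plan that is not shown.** True. But section 3.9 itself fixes the pooled t-test and the imbalance-only covariate rule, and both bypass the stratum.

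**Conclusion.** The point holds in a limited form. The protocol enrols people with minimal symptoms and stratifies randomisation by severity, then specifies an outcome analysis that ignores the stratum. If many scores lie near zero, a coaching benefit of 0.52 SD stopped at the floor would appear as d of about 0.40-0.48, with 59-73% power. A null pooled result on its own would then not separate absent benefit from benefit that could not be measured. How many scores will lie near zero is an assumption. Section 1.2 describes depression and anxiety as more common in this population, so the share could be smaller than in the lowest scenario.

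The documents do not support two stronger readings: that the sample-size statement is wrong, or that the pooled effect is the wrong main estimate. The gain on offer is modest: about 7-10 points of pooled power under the stated assumptions, and intervals by severity that help a reader interpret a null.

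**What to change.** In section 3.9:

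1. Keep the eligibility rule and the pooled coaching effect as the main estimate for PHQ-9 and GAD-7. Take it from a linear regression that always includes the section 3.6 severity stratum, whether or not the arms look imbalanced. The simple t-test can be reported beside it.
2. Add an arm-by-stratum model. Report the coaching effect with 95% CI in each stratum, as defined in section 3.6, as a pre-specified supportive analysis next to the pooled estimate.
3. State that a null pooled difference will be interpreted together with these intervals, and that they are estimates, not a powered test.
4. Leave the 0.52 sentence as it is, and do not move the effectiveness conclusion to the moderate-to-severe stratum.

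**Cost.** A few sentences, one covariate and one interaction term; no new patients, visits or data, because the stratum is already recorded for randomisation. The downside is wide stratum intervals: with roughly 19-44 of 120 in the upper stratum, half-widths are about 0.6 to 0.9 SD, and a null there would also be inconclusive.
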